## 6. PARTICIPANT IDENTIFICATION

### 6.1 Study Participants

Participants are eligible for randomization if they satisfy all the inclusion and exclusion criteria and their GP is agreeable to their participation.

### 6.2 Inclusion Criteria

- Male or Female, aged  $\geq 65$  years old.
- CHA2DS2-VASc score  $\geq 3$  in men or  $\geq 4$  in women (see Appendix 1)
- Participant is willing and able to give informed consent for participation in the study.

### 6.3 Exclusion Criteria

The participant may not enter the study if ANY of the following apply:

- Known to have AF or atrial flutter
- Latex allergy (given the potential for an allergic reaction to the Zio Patch).

## 7. STUDY PROCEDURES

### 7.1 Recruitment

GP practices (identified via local Clinical Research Networks and by direct approach) will identify eligible patients by running a predetermined electronic search of the practice database using the relevant local primary care software e.g. EMIS, SystemOne. An invitation letter, including an information leaflet, consent form, and Freepost return envelope, will then be sent by post (or, if

practical, electronically via email) by the GP. Web-based and written study information will be available to provide potential participants with further information to help them make an informed decision as to whether to participate. A 24-hour Freephone service (established by CTSU for other large heart disease trials) will be available for study participants, their carers or their doctors to discuss any aspects of the study with experienced clinical staff at the coordinating centre.

## **7.2 Enrolment and Eligibility Assessment**

There will be no face to face confirmation of eligibility. Participants will be asked to complete a baseline randomization questionnaire at the time of enrolment. This will include basic demographic information as well as medical information to confirm baseline CHA2DS2-VASc score (e.g. history of hypertension, stroke or diabetes, see Appendix 1).

## **7.3 Informed Consent**

All participants will be required to provide written informed consent by returning a completed consent form to the coordinating centre. Information for participants regarding the study will be available on the study website and in written form. There will be the option for telephone or email enquiries to be made to the study team for any questions prior to enrolment. It will be clearly stated that the participant is free to withdraw from the study at any time for any reason without prejudice to future care, without affecting their legal rights, and with no obligation to give the reason for withdrawal. The participant will be allowed as much time as wished to consider the information, and the opportunity to question the study team, their GP or other independent parties to decide whether they will participate in the study. The original signed consent form will be retained at the central coordinating office and a copy will be returned to all participants who subsequently go on to be randomized into the trial.

## **7.4 Randomization, blinding and code-breaking**

Participants who indicate on the randomization questionnaire that they are eligible and willing to join the trial, and provide written consent will be randomized by the central computer in CTSU, using a minimisation algorithm to ensure balance by important baseline variables.

Eligible patients will be randomized in a 1:1 ratio to a single 2-week ECG monitoring period with the Zio Patch versus usual care. The study will not employ a sham-patch and neither the trial team nor the participants will be blinded to the intervention. All participants will receive a letter informing them which group they have been assigned to. The participant's GP will be notified that the participant has been randomized and the study arm; a copy of the participant's consent form (signature page) will also be included for reference. For all participants screened with the Zio Patch, GP's will be sent the ECG findings related to the presence and duration of AF episodes, along with any details that might be useful to interpret these results (such as the duration of monitoring). Participants will also be sent this results letter, along with a cover letter. Future management of the monitoring results will be at the GPs discretion. Additional findings will also be communicated to GPs if considered to be clinically important. A complete monitoring report (including all incidental findings) will not be routinely provided to GPs but will be available if required.

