**Figure 2: Estimated cumulative percent of participants diagnosed with AF**

[figure not shown]

Based on these assumptions, a sample size of 1250 per arm (2500 participants) would give more than 90% power to detect the estimated difference in proportion with a diagnosis of AF at 2.5 years of 1.75% versus 4.4% (ratio of about 2.5) at  $2p < 0.05$  (see Appendix 2). Therefore, the initial overall sample size was set at 2500 participants.

As recruitment progressed, it became apparent that the trial would be able to achieve its initial target sample size without exhausting the available pool of interested GP practices, offering the possibility of extending recruitment in a cost-effective way. Based on over 1250 participants randomized before 1st February 2021 and their observed adherence to wearing the patch and AF detection rates by patch, a larger sample size of up to 5000 participants provides increased reassurance regarding a lower than anticipated AF rate ratio (e.g. around 3000 participants would

be required to maintain >90% at  $2p < 0.05$  if the ratio were to be 2 instead of 2.5 as predicted, with 4100 participants required to maintain >90% power at  $2p < 0.01$ ). Furthermore an increase in sample size allows for reliable assessment of the effects of screening for SCAF in the proposed subgroups (by age and by sex).

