### 8.3 Analysis of outcome measures

The fundamental assessments of efficacy will involve an “intention-to-treat” analysis among all randomized patients of allocation to screening versus allocation to usual care, irrespective of compliance.

Analysis of the primary outcome:

- The chi-square test will be used to compare the proportion of participants diagnosed with AF at 2.5 years of follow up in all those randomized to screening versus all those randomized to usual care.

Analysis of the secondary outcomes:

- The chi-square test will be used to compare the proportion of participants diagnosed with AF at 2.5 years of follow up in those randomized to screening versus those randomized to usual care separately by age subgroups of <80 and ≥80 years and by sex subgroups at randomization, with a test for heterogeneity of the results between the two subgroups.
- Mean durations of time with AF diagnosed after 5 years of follow-up from randomization in all those randomized to screening compared to all those randomized to usual care will be compared using a permutation test to assess statistical significance (in the overall cohort and, separately, by age subgroups of <80 and ≥80 years and by sex subgroups at randomization, with a test for heterogeneity between the two subgroups). Those with no diagnosis of AF by the end of the study will contribute zero time with AF.

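### Allocation is by minimisation on baseline variables, but the primary test is fixed as an unadjusted chi-square: valid, very slightly conservative, and improvable at no cost

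*Protocol*

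**What the plan says.** **Allocation.** Protocol section 7.4 says "Eligible patients will be randomized in a 1:1 ratio", by a central computer "using a minimisation algorithm to ensure balance by important baseline variables". The protocol does not name the variables.

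**Baseline data.** Section 7.2 describes a randomization questionnaire completed by every participant: "This will include basic demographic information as well as medical information to confirm baseline" (the score meant is CHA2DS2-VASc). Candidate covariates are therefore already collected.

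**Primary test.** Section 8.3: "The chi-square test will be used to compare the proportion of participants diagnosed with AF at 2.5 years". The comparison is between the two arms in the whole trial population, and no stratification or adjustment is mentioned.

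**Secondary tests.** The same chi-square comparison is made "separately by age subgroups of <80 and ≥80 years and by sex subgroups at randomization", with heterogeneity tests. Mean times with AF diagnosed after 5 years "will be compared using a permutation test to assess statistical significance". The protocol does not say how allocations are re-drawn in that permutation test.

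**The concern.** Minimisation forces the arms to agree closely on the balanced variables. If those variables predict the outcome, part of the chance difference between arms that would arise under simple randomization can no longer occur. An unadjusted chi-square still counts that part in its variance. Its reference distribution is then too wide, its p-values are a little too large, and some precision is given away.

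Table 4 in Appendix 2 shows that at least two baseline variables predict AF detection. The expected active-arm rate at 2.5 years is 3.27% below age 80 and 7.39% from age 80, and 5.82% in men and 3.64% in women. At stake is efficiency and agreement between design and analysis, not validity.

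**Working it through.** **1. The plan's own figure.** Table 2 gives 1914 participants in total for 1.75% versus 4.41% at 90% power and two-sided 0.05. The usual two-proportion formula with pooled null variance and continuity correction gives about 1918 (959 per arm); without the correction it gives 1770. For a ratio of 2 (2.205% versus 4.41%) the corrected formula gives 2940, against 2939 in Table 3. The stated figures therefore reproduce as those of an unadjusted comparison.

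**2. Inputs (Table 4).**

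| Group | Share | Active arm | Control arm (implied) |
|---|---|---|---|
| Age <80 | 64% | 3.27% | 1.31% |
| Age ≥80 | 36% | 7.39% | 2.95% |
| Men | 54% | 5.82% | 2.33% |
| Women | 46% | 3.64% | 1.46% |

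Assumptions that the protocol does not supply: age 80 and sex are minimisation factors; they are independent; their effects on the AF rate multiply.

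**3. Share of outcome variance explained.** For a two-level factor with shares w and 1−w and rates p1 and p2, R² = w(1−w)(p1−p2)² / [p(1−p)], where p is the weighted mean rate.

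- Age, active arm: p = 0.0475; 0.64 × 0.36 × 0.0412² / (0.0475 × 0.9525) = 0.00039 / 0.0453 = 0.86%.
- Sex, active arm: p = 0.0482; 0.54 × 0.46 × 0.0218² / (0.0482 × 0.9518) = 0.00012 / 0.0459 = 0.26%.
- Active arm together: about 1.1%.
- Age, control arm: p = 0.0190; 0.64 × 0.36 × 0.0164² / (0.0190 × 0.9810) = 0.33%.
- Sex, control arm: p = 0.0193; 0.54 × 0.46 × 0.0087² / (0.0193 × 0.9807) = 0.10%.
- Control arm together: about 0.4%.

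With the two arms' rates averaged, as for a null calculation, age gives 0.6%, sex 0.2% and the four age-by-sex cells jointly 0.8%.

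**4. True size of the unadjusted test.** Size = 2 × [1 − Φ(1.96 / √(1 − R²))]. With R² = 0.8%: 1.96 / √0.992 = 1.968, so the size is 0.0491.

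**5. Power, unadjusted versus stratified (no continuity correction, two-sided 0.05).**

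| Setting | R² | Unadjusted | Stratified |
|---|---|---|---|
| N = 2500, ratio 2.5, Table 4 rates | 0.8% | 97.89% | 97.93% |
| N = 2500, ratio 2, active rate 4.41% | 1.1% | 87.1% | 87.3% |
| N = 5000, ratio 2.5, Table 4 rates | 0.8% | 99.99% | 99.99% |

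The second row applies the active-arm R² to both arms, so it errs towards a larger gain.

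**6. Simulation.** Minimisation on age 80 and sex at N = 2500, comparing the chi-square with the Cochran-Mantel-Haenszel test:

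- Null rejection was 4.76% versus 4.77% (20,000 runs, Monte Carlo standard error about 0.15 points). That is too coarse to show a 0.1-point effect.
- The variance of the test statistic was 0.981 versus 0.988, a ratio of 0.993. This fits an R² of about 0.8%.
- Power at ratio 2, with an active rate of about 4.75%, was 90.0% versus 90.1% (8,000 runs).

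**7. Sensitivity.** Other factors might predict more strongly, but the protocol gives no AF rates by CHA2DS2-VASc score or by continuous age. For assumed values (N = 2500, ratio 2): R² of 2% gives size 0.0477 and a gain of 0.4 points; R² of 5% gives size 0.0443 and a gain of 1.0 point.

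**The case against.** The strongest reply is that nothing here is wrong. A chi-square test on all randomized participants is a valid test of the stated outcome. It does not inflate the type I error, and the effect is too small to change any conclusion. At 5000 participants Table 3 already gives 99 to 100% power at 2p<0.05. An adjusted supporting analysis may also stand in the statistical analysis plan, which is not shown. All of this stands, and it limits the point to a minor improvement. It does not remove it: the protocol itself names the primary test, and an analysis plan could not replace that test without departing from section 8.3.

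Three stronger readings are tempting and are not supported.

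- **That the permutation test ignores the design.** Section 8.3 gives no re-allocation scheme, so a permutation that re-runs the minimisation fits the text as well as a free shuffle does.
- **That all secondary tests ignore the balanced variables.** The subgroup analyses split by age and by sex one at a time, so each conditions on one of the two variables considered here.
- **That the loss is greatest in the weakly powered subgroups.** On the same assumptions as above, the active-arm R² is lower within subgroups than overall: about 0.65% for age among women and about 0.17% for sex among those under 80, against about 1.1% in the whole arm.

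**Conclusion.** The point holds as a minor one. Section 7.4 balances the arms on baseline variables, and section 8.3 fixes a primary test that does not use them. The test is valid and errs very slightly on the conservative side. If age 80 and sex are among the unnamed factors, are independent and act multiplicatively, the true size is about 0.049 instead of 0.05 and the power forgone is about 0.2 percentage points or less. Assumed stronger factors, with R² up to 5%, bring the gain to about 1 point at N = 2500 and ratio 2. A reader should not infer that the primary result would be unreliable or that the trial's sample size is affected.

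**What to change.** In section 8.3:

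- Name the minimisation factors, or refer to where they are listed.
- Make the primary test a Mantel-Haenszel test stratified by those factors, or a logistic model adjusted for them that reports a standardised risk difference or risk ratio. Keep the crude chi-square as a supporting result.
- State that the permutation test for mean time with AF respects the allocation scheme, by permuting within strata of the factors or by re-running the minimisation.

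The cost is a few sentences and a few lines of code. No new data are needed, because section 7.2 already collects demographics and the score components, and the sample size tables can stay as they are. In a trial without blinding, fixing this in advance also closes off a later choice between crude and adjusted results.

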### 7.5 Zio Patch administration

For those participants randomized to receive the Zio Patch, the device will be posted to their home address with instructions on how to apply and care for it. Email and Freephone telephone advice lines will be available for those who need support or encounter problems.

Participants will be asked to wear the Zio Patch continuously for 2 weeks. A return envelope will be provided so that, once the two week period is completed, participants can post back the device for analysis. If participants do not return the device, efforts will be made by the research team to contact them to encourage them to return the device.

### 7.6 EQ-5D questionnaires

In order to inform the planned cost-effectiveness analyses, randomized participants will be asked to self-complete an EQ-5D questionnaire (either via postal or digital methods) once recruitment has been completed and at about 2.5 years afterwards.

### 7.7 Discontinuation/Withdrawal of Participants from Study

Each participant has the right to withdraw from the study at any time, which will be made clear during the consent process. Any withdrawals will be recorded in the study database, including, where available, the reason for doing so.

### 7.8 Definition of End of Study

The end of study is defined as the date of the last electronic data download (from either central registries (NHS Digital) or from a participating GP practice. For the primary comparison, data will be sought at 2.5 years after randomization. For the secondary outcome of mean times with AF, further data will be sought at 5 years after randomization. However it is intended to continue to request longer-term data from NHS Digital (for up to 25 years after randomization) in order to undertake longer-term exploratory assessments of the clinical impact of allocation to screening (see Section 8.4).

## 8. STATISTICS AND ANALYSIS

### 8.1 Initial assumptions

**Study duration:** Logically, the length of the study should be the proposed time between screenings if this were put into practice. This will be achieved through the assessment of the secondary outcome of mean times with AF diagnosed at 5 years. However, a follow-up period of 25 years is proposed in AMALFI to allow for further research.

**AF detection with usual care (opportunistic screening):** The rate of opportunistic detection of AF in this population is unclear. Data from a 2014/2015 screening initiative across Dorset Clinical Commissioning Group reported opportunistic detection of SCAF in 0.7% of 61,000 people over the age of 65 who had a one-off pulse check while attending a flu clinic. However the proportion of attendees receiving a pulse check varied considerably between practices, ranging from 8% to 78% of individuals, with an average of 51%. So, among all those aged  $\geq 65$  years old SCAF may only be detected opportunistically in about 0.3-0.4% per annum.

The AMALFI population (with elevated CHA2DS2-VASc score) will tend to be at somewhat higher risk of SCAF, and so we anticipate that usual care with opportunistic screening by the GP may identify AF in about 0.7% per annum.

**AF detection with screening:** The incidence of SCAF detection by screening with Zio Patch is unknown in this high risk population. Among 7000 people aged 75 screened with intermittent ECGs over a 2-week period, the rate of detection of SCAF was about 3%. However, in AMALFI the monitoring will be continuous for two weeks (likely to provide higher rates of detection). Taking into account a moderate level of non-compliance with the patch, we estimate that a two-week screening with Zio Patch may lead to a diagnosis of AF in around 3.75% participants. Details of the assumptions and modelling of the rates for the purposes of the statistical power calculations can be found in appendix 2.

**AF detection after the screening period:** In the screening group it is anticipated that further cases will continue to be identified by usual care after screening. These rates are assumed to increase with time from screening to converge with the rate found by usual care (0.7% per annum) and range from 0.2% during the first year following randomization, to 0.5% during the fifth year (see Appendix 2).

## 8.2 Sample size and predicted number of diagnoses

Given the assumptions above, the expected prevalence of AF over time in the AMALFI trial is shown in Figure 2 (see Appendix 2 for statistical model and calculations).

**Figure 2: Estimated cumulative percent of participants diagnosed with AF**

[figure not shown]

Based on these assumptions, a sample size of 1250 per arm (2500 participants) would give more than 90% power to detect the estimated difference in proportion with a diagnosis of AF at 2.5 years of 1.75% versus 4.4% (ratio of about 2.5) at  $2p < 0.05$  (see Appendix 2). Therefore, the initial overall sample size was set at 2500 participants.

As recruitment progressed, it became apparent that the trial would be able to achieve its initial target sample size without exhausting the available pool of interested GP practices, offering the possibility of extending recruitment in a cost-effective way. Based on over 1250 participants randomized before 1st February 2021 and their observed adherence to wearing the patch and AF detection rates by patch, a larger sample size of up to 5000 participants provides increased reassurance regarding a lower than anticipated AF rate ratio (e.g. around 3000 participants would

be required to maintain >90% at  $2p < 0.05$  if the ratio were to be 2 instead of 2.5 as predicted, with 4100 participants required to maintain >90% power at  $2p < 0.01$ ). Furthermore an increase in sample size allows for reliable assessment of the effects of screening for SCAF in the proposed subgroups (by age and by sex).

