| Study Design        | Randomized controlled trial                                                                                                                                                                                                                                                                                                                                                                                                                                                                            |
| Study Participants  | Individuals with a CHA 2 DS 2 -VASc score $\geq 3$ (men) or $\geq 4$ (women), aged $\geq 65$ years without known atrial fibrillation (AF) identified from primary care records.                                                                                                                                                                                                                                                                                                  |
| Planned Sample Size | At least 2500 and up to 5000 (including up to 2500 randomized to the Zio Patch and 2500 to the control arm)                                                                                                                                                                                                                                                                                                                                                                                            |
| Primary Objective   | To assess the effect of 2 weeks of continuous monitoring using Zio Patch on the proportion of participants diagnosed with AF compared to usual care at 2.5 years of follow up from randomization (i.e. at around the midpoint of a proposed 5-year screening interval).                                                                                                                                                                                                                                |

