### **Sample size calculation:**

Table 2 below gives a set of power calculations based on the expected proportions diagnosed with AF at half yearly points up to 5 years. It is assumed that participants are randomized 1:1 to give to equal numbers in the control and active arms. The 2.5 year row is highlighted as being a suitable mid-study comparison time point for a proposed screening interval of 5 years.

Table 3 provides a summary of power calculations for different samples sizes made possible by an extension in recruitment of up to 5000 participants for the whole cohort and under different assumptions regarding AF detection ratios. Table 4 provides the same calculations for different age and sex subgroups.

**Table 1 – initial projections for proportions of new AF cases found in the active and control groups at different time points**

| Year end | Placebo arm                                     |                                                           | Active arm                                                                                    |                                      |                                                                                   |                                                                                                                                                    |                                                           |
|----------|-------------------------------------------------|-----------------------------------------------------------|-----------------------------------------------------------------------------------------------|--------------------------------------|-----------------------------------------------------------------------------------|----------------------------------------------------------------------------------------------------------------------------------------------------|-----------------------------------------------------------|

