**Table 4 – power and sample size calculations for subgroup analyses by age and sex**

| Assumptions |                              |                                                      |                                                                      |                                                    |                                                               | Resulting power and sample sizes              |                                                      |                                            |                                            |                                            |                                            |
|--------------------|------------------------------|------------------------------------------------------|----------------------------------------------------------------------|----------------------------------------------------|---------------------------------------------------------------|------------------------------------------------------|------------------------------------------------------|--------------------------------------------|--------------------------------------------|--------------------------------------------|--------------------------------------------|
| Group       | Percent of population | AF rate detected through patch in active arm* | Total AF rate in active arm at 2.5 years (patch rate x 1.177) | Ratio of AF rates in active vs control arms | Implied AF rate in controls (based on detection ratio) | n needed in subgroup for 90% power, p<0.05 | n needed in subgroup for 90% power, p<0.01 | Power for total of 4000, 2p<0.05 | Power for total of 4000, 2p<0.01 | Power for total of 5000, 2p<0.05 | Power for total of 5000, 2p<0.01 |
| Age <80  | 64%                          | 2.78%                                                | 3.27%                                                                | 2.5                                         | 1.31%                                                         | 2642                                                 | 3658                                                 | 89%                                        | 73%                                        | 95%                                        | 85%                                        |

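### The reliable subgroup assessment claimed for 5000 participants is shown only at ratio 2.5; at ratio 2, the case used to justify the extension, power is about 72% in women and 82% under age 80

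*Protocol*

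**What the plan says.** The Synopsis sets the sample size at "At least 2500 and up to 5000 (including up to 2500 randomized to the Zio Patch and 2500 to the control arm"). Section 8.2 gives two reasons for going beyond the initial 2500. The first is that "a larger sample size of up to 5000 participants provides increased reassurance regarding a lower than anticipated AF rate ratio", with an example for the case "if the ratio were to be 2 instead of 2.5 as predicted". The second follows directly: "an increase in sample size allows for reliable assessment of the effects of screening for SCAF in the proposed subgroups", meaning the age and sex subgroups.

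The supporting figures are in Appendix 2. Table 3 covers the whole trial at ratios 2.52, 2.5 and 2. The text then states: "Table 4 provides the same calculations for different age and sex subgroups". Every row of Table 4 has ratio 2.5. In its column "Power for total of 5000, 2p<0.05" it prints 89% for women, 95% for age <80, 99% for age ≥80 and 99% for men.

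Section 8.3 plans the chi-square comparison "separately by age subgroups of <80 and ≥80 years and by sex subgroups at randomization, with a test for heterogeneity" between the two subgroups. Section 8.5.1 makes the split at age 75 exploratory because power under 75 would be limited even with 5000 participants.

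**The concern.** The lower ratio is one of the two reasons for the extension, yet it disappears at the point where the second reason depends on it. A reader told that Table 4 repeats Table 3's calculations would expect subgroup power at both ratios, and would take the claim of reliability to hold under the scenario just discussed.

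Power matters here because the protocol uses it to decide the standing of a subgroup: the age-75 split was made exploratory on that ground. Sections 3.6 and 3.7 say that results by age and sex should inform the choice of population for screening. If the ratio is near 2, a non-significant result in women would be fairly likely by chance. It could then be misread as evidence against screening in a subgroup that the plan says it can assess reliably.

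**Working it through.** **Inputs.** These come from Table 4: share of the population, interim patch detection rate, and the multiplier 1.177 that converts the patch rate to the active-arm rate at 2.5 years. Allocation is 1:1 (section 7.4). The continuity correction is stated in Table 2, and Tables 3 and 4 follow it. For ratio 2, I use Table 3's convention: the active rate is held and the control rate is active rate ÷ ratio (4.41% against 2.21% in Table 3).

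**Formulas.** With total T and share f, n = T × f / 2 per arm and d = pA − pC. The corrected effective size is n* = (n − 1/d)² / n. With p̄ = (pA + pC)/2,

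power = Φ{ [d√n* − z√(2p̄(1−p̄))] / √(pA(1−pA) + pC(1−pC)) }, where z = 1.960 for 2p<0.05 and 2.576 for 2p<0.01.

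**Reproducing the plan (women, ratio 2.5, T = 5000).**
- n = 5000 × 0.46 / 2 = 1150
- pA = 3.09% × 1.177 = 3.637%; pC = 3.637% / 2.5 = 1.455%; d = 0.02182; 1/d = 45.8
- n* = (1150 − 45.8)² / 1150 = 1060
- power = Φ[(0.7105 − 0.4366) / 0.2222] = Φ(1.23) = 89.1%; the table prints 89%
- total for 90% power: 2366 women; the table prints 2367

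The other three subgroups reproduce as well (5000, 2p<0.05): age <80 94.9% (printed 95%), age ≥80 98.6% (99%), men 99.4% (99%). So does Table 3 at ratio 2 with the 3.75% patch rate: 2938 for 90% power (printed 2939), and 99.0% power at 5000 (printed 99%).

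**Same method at ratio 2 (women, T = 5000).**
- pA = 3.637%; pC = 1.818%; d = 0.01818; 1/d = 55.0
- n* = (1150 − 55.0)² / 1150 = 1043
- power = Φ[(0.5872 − 0.4515) / 0.2300] = Φ(0.59) = 72.2%
- total for 90% power: 3586 women, against 0.46 × 5000 = 2300 available

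| Subgroup (T = 5000) | Printed, ratio 2.5 (2p<0.05 / 0.01) | Ratio 2, corrected | Ratio 2, uncorrected |
|---|---|---|---|
| Women | 89% / 75% | 72% / 49% | 76% / 54% |
| Age <80 | 95% / 85% | 82% / 62% | 85% / 66% |
| Age ≥80 | 99% / 95% | 91% / 77% | 93% / 80% |
| Men | 99% / 98% | 95% / 85% | 96% / 87% |

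**Sensitivity.** If ratio 2 arises instead from a lower active rate with women's control rate held at 1.455%, power in women is 61% (67% uncorrected). The 5000 is a ceiling: at 4000 and ratio 2, corrected power is about 61% in women and 72% under 80.

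**The 5000, 2p<0.01 column at ratio 2.5.**
- Age <75: n = 625, pA = 2.966%, pC = 1.186%, d = 0.01780, n* = 518, power 28.5%; printed 34%. The row's other power cells, printed 41%, 20% and 52%, come out at 41.7%, 20.4% and 51.9%. Varying the rounded 25% share from 24.5% to 25.5% gives only 27.7% to 29.3%. The uncorrected figure, 35.6%, does not match either.
- Women: 73.1%; printed 75%. Varying the share from 45.5% to 46.5% gives 72.5% to 73.7%. Uncorrected: 77.3%.
- Age <80 (84.6%, printed 85%), age ≥80 (94.2%, printed 95%), men (97.3%, printed 98%) and age ≥75 (99.5%, printed 100%) agree within one point.

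**The case against.** Table 4 prints its ratio in every row, and 2.5 is the predicted ratio. The sentence in section 8.2 compares a larger trial with a smaller one and does not say that it holds at ratio 2. By the same method at ratio 2.5, going from 2500 to 5000 raises power from 58% to 89% in women and from 69% to 95% under 80, a real gain. The protocol sets no threshold for reliability. At ratio 2, three of the four subgroups still have 82% to 95%. The planned chi-square test is not said to be continuity corrected, and without the correction women have 76%. Section 8.3 also pairs the subgroup tests with a test for heterogeneity, so inference does not rest on separate p-values alone.

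All of this stands, and it limits the point. It does not remove it: the uncorrected figure in women is still below 80%, and the text promises the same calculations as Table 3 but omits the ratio that Table 3 adds.

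Stronger readings are tempting but not supported. A reader might infer that Table 4's main power figures are wrong; they are right at 2p<0.05 for their stated ratio. A reader might infer that all subgroups are underpowered; men and those aged 80 or over keep more than 90% at 2p<0.05. A reader might treat the absence of power for the heterogeneity test, or for all subgroup tests succeeding together, as a contradiction. The protocol makes no claim about either, and joint power would need an age-by-sex distribution that it does not give. The interim rates are openly labelled as interim, so their imprecision is not an error.

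**Conclusion.** The point holds as an unsupported sensitivity claim, with two wrong table cells beside it. Under the ratio that section 8.2 itself raises, 5000 participants do not give women the power that the sentence implies, and support is only partial under age 80. The 72% and 82% rest on two-sided 0.05, the full 5000, Table 4's shares and interim rates, the continuity correction, and a ratio of 2 reached by a higher control rate. Women stay below 80% under the other two variants run at 5000.

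The age <75 cell overstates power by about 6 percentage points (34% against 28%) and the women's cell by about 2 (75% against 73%). The first concerns an exploratory subgroup and changes no decision. The primary analysis is not affected: whole-trial power at ratio 2 and 5000 is 99%, as Table 3 says.

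**What to change.** 1. Add ratio-2 rows to Table 4 for the four secondary subgroups (women, men, age <80, age ≥80), on the same basis as Table 3.
2. Make the sentence in section 8.2 conditional: 5000 participants give about 89% power or more per subgroup at 2p<0.05 if the ratio is 2.5, but about 72% in women and 82% under age 80 if it is 2.
3. Recompute the total-5000, 2p<0.01 column of Table 4, including about 28% for age <75 and about 73% for women.

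The cost is four table rows, one reworded sentence and one recalculated column. Stated subgroup power becomes less favourable. Sample size, outcomes and analyses stay as they are.
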